## Abstract

**Background:**

Diarrhoeal disease is a major global health problem, particularly affecting children under the age of 5 years. Besides oral rehydration solution, probiotics are also commonly prescribed to children with acute watery diarrhoea in some settings. Results from randomised clinical trials (RCTs) in which investigators studied the effect of probiotics on diarrhoeal symptoms have largely shown a positive effect; yet, the overall quality of the data is limited. In Vietnam, probiotics are the most frequently prescribed treatment for children hospitalised with acute watery diarrhoea, but there is little justification for this treatment in this location. We have designed a RCT to test the hypothesis that an oral preparation of *Lactobacillus acidophilus* is superior to placebo in the treatment of acute watery diarrhoea in Vietnamese children.

**Methods:**

This RCT was designed to study the effect of treatment with *L. acidophilus* (4 × 10^9^ colony-forming units/day) for 5 days for acute watery diarrhoea against a placebo in 300 children ages 9 to 60 months admitted to hospitals in Vietnam. Clinical and laboratory data plus samples will be collected on admission, daily during hospitalisation, at discharge, and at follow-up visits for a subset of participants. The primary end point will be defined as the time from the first dose of study medication to the start of the first 24-hour period without diarrhoea as assessed by the on-duty nurse. Secondary endpoints include the time to cessation of diarrhoea as recorded by parents or guardians in an hourly checklist, stool frequency over the first 3 days, treatment failure, rotavirus and norovirus viral loads, and adverse events.

**Discussion:**

The existing evidence for the use of probiotics in treating acute watery diarrhoea seems to favour their use. However, the size of the effect varies across publications. An array of different probiotic organisms, doses, treatment durations, study populations, designs, settings, and aetiologies have been described. In this trial, we will investigate whether probiotics are beneficial as an adjuvant treatment for children with acute watery diarrhoea in Vietnam, with the aim of guiding clinical practice through improved regional evidence.

**Trial registration:**

Current Controlled Trials ISRCTN88101063

## Background

Diarrhoeal disease is a global health issue, yet the vast burden is in young children in developing countries [1]. In 2010, more than 7 million children younger than 5 years old died, and 15% of these deaths were attributed to diarrhoea [2,3]. Typically, diarrhoeal episodes are self-limiting, and patients often recover without receiving an aetiological diagnosis. In those who are diagnosed, rotavirus is the most frequently identified pathogen, followed by a multitude of other viral, parasitic and bacterial agents [4]. Vietnam is a rapidly developing country in Southeast Asia, with an estimated mortality rate of 23 per 1,000 live births among children younger than 5 years old [2]. The number of deaths in children in this key age bracket in Vietnam in 2010 was 34,940, 11% of which were attributable to diarrhoeal infections [3].

Oral rehydration solution (ORS), zinc and antimicrobials are the main treatments for acute diarrhoea in children in Vietnam [5]. During a cross-sectional study of approximately 1,500 children hospitalised with diarrhoea, however, we found that 11% of diarrhoeal patients were given probiotics prior to hospitalisation, and 71% of children were prescribed probiotics during hospitalisation ([name] *et al.*, unpublished manuscript). Probiotics are preparations of bacteria and yeasts that are considered to confer a beneficial health effect when taken in an adequate amount [6]. Probiotics have been studied extensively for their effects in preventing and treating a multitude of conditions, including the treatment of lactose intolerance, traveller’s diarrhoea and the prevention and treatment of nosocomial diarrhoea [7-10]. In acute diarrhoea, a reduction in the frequency of diarrhoeal symptoms has been reported in adults and children treated with probiotics. This cessation of diarrhoeal symptoms has been observed specifically in patients with rotavirus, in those treated during the early stages of a disease episode, and in those treated with *Lactobacillus* spp. [11-14]*.* Investigators in previous trials have evaluated the effect of probiotic colonisation on rotavirus and found a potential reduction in rotavirus-shedding in cohorts of Taiwanese, Polish and Italian children [15-17]. Probiotics are well-tolerated; adverse events (AEs) are rare and generally occur in patients with underlying chronic diseases or in those on immunosuppressive therapy [18,19].

In a Cochrane review of the effect of probiotics for the treatment of acute watery diarrhoea, Allen *et al.* combined data from 8,014 participants in 63 studies [20]. The authors noted extensive heterogeneity in study design, definitions, infecting agents, probiotic organisms and dosage. Notwithstanding these caveats, the meta-analysis found probiotics to be effective in reducing the duration of diarrhoea by a mean of 24.76 hours (95% confidence interval (CI) = 15.9 to 33.6 hours) compared to patients who either did not receive probiotics or were given a placebo. On the basis of these same analyses, probiotic therapy was found to reduce the frequency of stools on the second day of treatment by a mean of 0.8 stools (95% CI = 0.45 to 1.14), and it reduced the risk of developing persistent diarrhoea by 59% (95% CI for risk ratio = 0.32 to 0.53). `The authors recommended the design of larger, more robust trials specifically focusing on pathogen identification and the incorporation of standard definitions and end points to inform clinical guidelines.

There is currently no international regulatory agreement for the manufacturing or the clinical use of probiotics, and there are different levels of scientific evidence required to substantiate the health benefits of probiotics [21-23]. This evidence is dependent on the product, the specific disease effects, the strain and the dose. Additionally, probiotics can be classified as either food additives or drugs, depending on the local regulatory authority. This discrepancy has led to interchangeable and often nonstandardised therapeutic use. Therefore, trials incorporating the recommendations from Allen *et al.*[20] to investigate the effects of probiotics for acute diarrhoea are vital to increase the evidence base for the use of probiotics as a clinical therapy in similar settings.

## Methods/design

### Study aims

We hypothesise that *L. acidophilus* is superior to no *L. acidophilus* in the treatment of children admitted to the hospital for acute watery diarrhoea in Ho Chi Minh City, Vietnam. We will test this hypothesis by comparing an oral daily dose of 4 × 10^9^ colony-forming units (CFUs) of *L. acidophilus* against placebo in children hospitalised with acute diarrhoea. The study design presented herein aims to investigate whether probiotic therapy with *L. acidophilus* should be used as an appropriate and efficacious adjuvant to ORS and zinc in treating children hospitalised with acute watery diarrhoea. Using these data, we additionally aim to inform local clinical practice on the use of probiotics for treating acute diarrhoea by improving the quality of clinical evidence.

### Study design

This study is a multicentre, randomised, double-blind, placebo-controlled trial designed to assess the effect of adjunctive probiotic (*L. acidophilus*) therapy in children admitted to the hospital with acute watery diarrhoea. Laboratory endpoints from admission until discharge will be recorded, and colonisation will be assessed in an outpatient follow-up visit with the first 50 subjects who agree to prolonged participation.

### Eligibility

To be eligible for enrolment, patients will need to be between 9 and 60 months of age and require hospitalisation for acute, nonbloody, nonmucoid, watery diarrhoea with a history of less than 3 days, and written informed consent from a parent or guardian will be required. This age group was selected, as healthy children younger than 9 months of age have less solid stools than those in an older age category, making the cessation of diarrhoeal symptoms more difficult to assess. *Diarrhoea* in this study is defined according to the criteria of the World Health Organisation (WHO): the passage of unusually loose or watery stools at least three times within a 24-hour period [5]. According to the Bristol Stool Form Scale, the aspect of the stool will be defined as watery with no solid matter (type 7 stool form) [24].

Patients who meet any of the following criteria will not be eligible for participation in the study: at least one episode of diarrhoeal disease in the month prior to admission, those taking an antiemetic or antidiarrhoeal medication at the time of presentation, those who are known to have short bowel syndrome, those with an underlying chronic inflammatory gastrointestinal disease, those who are immunocompromised or immunosuppressed, those who are on prolonged steroid therapy and those who are severely dehydrated (according to the definitions of the WHO guidelines for the treatment of diarrhoea) [5].

### Inclusion of patients and informed consent

A physician at each participating centre will approach all parents or guardians of patients who meet all the inclusion criteria and none of the exclusion criteria after routine admission. Informed consent will be sought from parents or guardians (Figure 1). If parents or guardians are indecisive about enrolment, they will be given until 72 hours after disease onset to consider entry into the study, after which point the patient will no longer be eligible.

**Figure 1 F1:**
[figure not shown]
**Trial study flow**-**chart.**

### Study medication and quality control

The study medication (lyophilised *L. acidophilus*, manufactured under the WHO good manufacturing process guidelines) will be purchased from Imexpharm Pharmaceutical Joint Stock Corporation (Cao Lanh, Vietnam). This probiotic is registered with the Vietnam Ministry of Health (MOH) as a drug. The laboratories at Oxford University Clinical Research Unit will perform internal quality control of the medication before the start of the study. Sachets will contain 1 × 10^9^ CFU of *L. acidophilus*. Placebo sachets will contain an excipient (maltodextrin) only. The manufacturer will blind the contents of the sachets, and the master code will be disclosed to the study pharmacist only.

### Treatment groups and duration of treatment

All patients will receive the standard of care, according to the national guidelines for the management of diarrhoeal diseases in children (Vietnam MOH, 2009), supplemented with oral zinc (20 mg per day) for 10 days, according to the WHO guidelines [5]. Subsequently, all patients will be randomly assigned to one of the two study groups at a 1:1 ratio. As probiotics are widely used without adverse effects and scientific publications indicate a variable beneficiary effect, the standard dose of study medication has been increased to avoid underdosing. Therefore, one group of participants will receive twice the standard daily dose of *L. acidophilus* (4 × 10^9^ CFU), and the other group of participants will receive placebo. The regimes will be identical in both study groups: doses every 12 hours for 5 days. For each dose, two sachets of the study medication will be dissolved in 10 ml of water and will be administered orally to participants by their parents or guardians. If the participant vomits within 60 minutes of taking the drug, an additional dose will be given (up to two extra doses in 4 hours). Dosing and redosing will be recorded in the case report form (CRF).

If participants require an antidiarrhoeal or antiemetic medication, they will be categorised as a treatment failure and analysed accordingly. The prescription of any additional treatment, including antimicrobials, will be recorded in the CRF.

If treatment is discontinued because of an AE, the treating physician will record this and monitor the individual until the AE has resolved or stabilised. Participants who discontinue study treatment because of an AE will continue to be followed as per protocol. Physicians will discharge participants after the completion of the 5-day treatment course or 24 hours after the complete cessation of symptoms, whichever occurs first. If participants are discharged before completing the 5-day treatment course, the parents or guardians will be asked to complete the administration of all 10 doses. A follow-up visit at day 12 will be planned with the parents or guardians of participants upon discharge.

### Randomisation and blinding

The study pharmacist will create a computer-generated block randomisation with blocks of varying size and stratification by participating centre. The probiotic and placebo sachets will be prepared in 5-day treatment packages plus vomit doses as described below. These will be labelled in advance and kept in a secure location. Participant numbers, which correspond to a package of sachets, will be assigned to each enrolled patient in strict numerical sequence. The treatment packages will be dispensed according to the participant number once a patient is enrolled into the trial. A chronological log of all enrolled patients will be maintained, and the next available sequential study code will be assigned to patients as they enrol.

### Data collection

Data will be recorded on study-specific CRFs and samples will be collected from each participant as indicated in Table 1. Briefly, after enrolment, study staff will perform the assessments, complete the appropriate CRF sections and collect laboratory samples according to protocol. Study medication will then be assigned. During hospitalisation, daily assessments of the participants will be performed and study staff will collect daily faecal samples or rectal swabs. Once the treating physician has deemed hospitalisation is no longer required, discharge will be arranged, as well as a follow-up visit. On discharge and at follow-up, assessments will be performed and faecal samples collected.

**Table 1 T1:** Clinical and laboratory data collection

	**Admission**	**Daily**	**Discharge**	**Follow-up**
Physical examination	✓	✓	✓	✓
Assessment of dehydration	✓	✓	✓	✓
Assessment of diarrhoea	✓	✓	✓	✓
Data collection	✓	✓	✓	✓
Faecal sample	✓		✓*	✓*
Faecal or rectal swab		✓	✓*	✓*
Blood sample (3 ml) (biochemistry/haematology and viral polymerase chain reaction)	✓			

* If the participant cannot produce a stool sample on discharge, a faecal or rectal swab will be collected instead.

### Sample handling and storage

Samples will be labelled with the patient study code assigned at enrolment. The samples will be used for the purpose of this study, as stated in the protocol, then stored for future use. Consent will be obtained from participants’ parents or guardians for sample storage and/or shipment of specific samples to collaborating institutions for investigations that cannot be performed locally.

### Laboratory methods

During the study, all collected samples will be labelled as stated in the protocol, stored at 4°C and transported to the laboratory at the Oxford University Clinical Research Unit within 24 hours. Routine haematology and biochemistry tests will be performed on blood samples at admission to evaluate the severity of dehydration and disease.

### Bacteriology

Faecal samples will be cultured on blood agar, MacConkey agar, xylose lysine desoxycholate agar, *Campylobacter* selective media and selenite cystine broth (Oxoid Microbiology Products; Thermo Scientific, Basingstoke, UK) to detect *Salmonella* spp.), *Shigella* spp. and *Campylobacter* spp. If pathogenic bacteria are suspected, isolation will be performed on nutrient agar (Oxoid Microbiology Products), followed by identification by standard biochemical reactions and API 20 E (bioMérieux, Marcy l’Etoile, France). Antimicrobial susceptibility testing will be performed on all pathogenic bacteria on Müller-Hinton agar by disk diffusion for ampicillin (10 μg), amoxicillin/clavulanic acid (20/10 μg), ceftriaxone (30 μg), ceftazidim (30 μg), ciprofloxacin (5 μg), nalidixic acid (30 μg), ofloxacin (5 μg), gentamicin (10 μg), chloramphenicol (30 μg) and trimethoprim/sulfamethoxazole (23.75/1.25 μg; Oxoid Microbiology Products). Erythromycin (15 μg) and clindamycin (2 μg) will be added for *Campylobacter* spp. Zone diameters will be interpreted according to the Clinical Laboratory Standards Institute (CLSI) clinical breakpoints. Culture results and antimicrobial susceptibility results will be reported back to the treating clinicians.

### Virology

Norovirus and rotavirus real-time reverse transcriptase polymerase chain reaction (RT-PCR) will be performed on total nucleic acid extracted from blood and faecal samples collected on admission using a previously published method [25]. Results will be reported to the treating clinician and disclosed to the parents or guardians of the participants. Aliquots of faecal samples collected at discharge and during follow-up visits will be stored as 10% vol/vol suspensions in phosphate-buffered saline at −80°C. Faecal or rectal swabs collected during hospitalisation will be stored at −80°C in viral transport media. Norovirus and rotavirus real-time RT-PCR will be performed in batches retrospectively. Because this trial is exploratory, results will be analysed for the patients who test positive for norovirus and/or rotavirus at admission only.

### Primary end point

The primary end point is the time from the first dose of study medication to the start of the first 24-hour period without diarrhoea as assessed by the nurse on duty.

### Secondary end points

The following are the secondary end points:

1. The time from the first dose of study medication to the start of first 24-hour diarrhoea-free period as recorded by parents or guardians in an hourly checklist, which will be collected by the nurses on duty every 12 hours.

2. Treatment failure, defined as the occurrence of (a) No resolution of diarrhoea after 5 days of treatment, (b) severe symptoms for which treatment is stopped, such as the development of severe dehydration, renal failure, (septic) shock, respiratory distress or other syndromes associated with diarrhoeal disease as complications (e.g., pneumonia) [5]; and (c) additional antiemetic (domperidone) or antidiarrhoeal (aluminium silicate or racecadotril) treatment.

3. The frequency of stools during the first 3 days after the first dose of study medication.

4. The load in copies per millilitre of viral transport medium of norovirus and rotavirus measured by RT-PCR, assessed daily from admission until discharge and at follow-up.

5. The duration of hospitalisation, defined as the number of days from hospital admission until discharge.

6. The extent of intestinal *L. acidophilus* colonisation, assessed by analyses of faecal samples or rectal swabs collected on admission, on discharge and at outpatient follow-up for the first 50 participants who agree to participate.

7. The number and severity of AEs.

### Reporting of serious adverse events

All AEs and serious adverse events (SAEs) will be recorded on the participant’s CRF. If a participant experiences a SAE, defined according to International Conference on Harmonisation of Technical Requirements for Registration of Pharmaceuticals for Human Use guidelines on clinical safety data management, the treating physician will inform the principal investigator and complete the specific CRF [26]. All SAEs will be reported as soon as possible to the Data Safety Monitoring Board (DSMB), the research ethics committees of reference and the Hospital Ethical Committee where the participant is admitted.

### Sample size and statistical considerations

Data originating from three hospitals in Ho Chi Minh City suggest that the median duration of hospitalisation in our target population is 5 days (interquartile range = 3 to 6 days; mean and standard deviation [SD] of log_10_ duration = 0.61 and 0.27, respectively) and an approximately normal distribution of the log-transformed data. As we have limited preexisting data on the overall length of diarrhoeal illness (prehospitalised and hospitalised), and as children are usually discharged at the time of resolution of diarrhoea, we used the variability of the length of hospitalisation as the basis of our sample size calculation using R software version 2.15.1. This study is designed to test the hypothesis that probiotic therapy is superior to placebo for the treatment of acute watery diarrhoea. It is powered to detect a 20% decrease in the duration of acute watery diarrhoea (corresponding to an absolute effect size of approximately 24 hours) of twice the standard dose of probiotics compared to placebo. For 80% power with a two-sided 5% significance level, a total of 123 participants per study group are required. To account for potential inadequacies in our assumptions and some loss to follow-up, the sample size was increased by 22%. Therefore, a total sample size of 300 participants (150 in each group) will be recruited.

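### The 80% power at 123 per group assumes every duration is fully observed; allowing for discharge by day 5 it is about 73% to 76%, and censoring takes much of the 22% margin

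*Protocol article*

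**What the plan says.** The section on sample size takes its variability from earlier hospital stays, with "mean and standard deviation [SD] of log_10_ duration = 0.61 and 0.27, respectively". The reason given is that "as children are usually discharged at the time of resolution of diarrhoea, we used the variability of the length of hospitalisation". The target effect is stated as follows: "It is powered to detect a 20% decrease in the duration of acute watery diarrhoea (corresponding to an absolute effect size of approximately 24 hours". The result is "For 80% power with a two-sided 5% significance level, a total of 123 participants per study group are required". The margin is then explained: "To account for potential inadequacies in our assumptions and some loss to follow-up, the sample size was increased by 22" per cent, which gives 150 per arm.

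Three other places bear on what can be observed:

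- **Primary end point:** time from first dose to "the start of the first 24-hour period without diarrhoea as assessed by the nurse on duty".
- **Treatment groups and duration of treatment:** "Physicians will discharge participants after the completion of the 5-day treatment course or 24 hours after the complete cessation of symptoms, whichever occurs first". A follow-up visit is planned for day 12.
- **Analysis and reporting:** a lognormal accelerated failure time (AFT) model that accepts right- and interval-censored times. The only censoring it names is for withdrawal or loss to follow-up; discharge with unresolved diarrhoea is not mentioned.

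**The concern.** No term for unobserved end points enters the calculation behind 123. Yet nurse assessment ends at discharge, by about day 5, and a full 24-hour clean period seen in hospital must begin by about day 4. The Discussion reports discharge times of 1 to 22 days in the earlier three-hospital study, with the same 5-day median, so the stays behind the SD of 0.27 appear not to have been cut at day 5. A child still ill at the limit contributes only a right-censored time. This censoring is scheduled and foreseeable, unlike dropout, and it falls on the children with the longest illness.

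Two things are at stake: whether the printed 80% at 123 is true of the planned analysis, and how much of the 22% is left for what it was added to cover.

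**Working it through.** **Inputs.** From the sample size section: log10 mean 0.61, SD 0.27, ratio 0.80 (δ = −log10 0.8 = 0.0969), two-sided 5%, 80% power. Nurse assessments are every 12 hours (Analysis and reporting; Discussion). Assumed here: hospital stay stands for time from first dose to the end point, and observation ends at day 5, or at day 4 if the whole 24-hour period must be seen in hospital.

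**1. The printed figure.** n = 2(1.960 + 0.842)² × 0.27² / 0.0969² = 121.9 per arm. The t-test version gives 122.8, rounded up to 123. Then 123 × 1.22 = 150.06. The figure is therefore a complete-data calculation, and the margin is 150 − 123 = 27 per arm.

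**2. Share censored.** P(T > c) = 1 − Φ((log10 c − μ)/0.27), with μ = 0.61 on placebo and 0.61 − 0.0969 = 0.5131 on probiotic.

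- Day 4: placebo 1 − Φ(−0.029) = 51%; probiotic 1 − Φ(0.330) = 37%; average 44%.
- Day 5: placebo 1 − Φ(0.330) = 37%; probiotic 1 − Φ(0.689) = 25%; average 31%.

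**3. Power.** The SE of the log10 ratio comes from the expected information of the two-arm lognormal AFT model (common scale, 12-hour grid, right-censoring at the limit). Power = Φ(0.0969/SE − 1.96). At 123 per arm the SE is 0.0346 with no limit, 0.0362 at day 5 and 0.0377 at day 4. For day 4, Φ(0.0969/0.0377 − 1.96) = Φ(0.61) = 73%. The column for 135 per arm is 150 less an assumed 10% loss.

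| log10 mean 0.61 | Power at 123 | at 135 | at 150 | n per arm for 80% |
|---|---|---|---|---|
| No limit | 80% | 84% | 87% | 123 |
| Day-5 limit | 76% | 80% | 84% | about 135 |
| Day-4 limit | 73% | 77% | 81% | about 146 |

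A simulation of 4,000 trials with exact event times agrees: at 123 per arm 80.5%, 77.0% and 73.7%; at 150 per arm 87.5%, 85.9% and 82.1%.

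**4. Margin consumed.** 135 − 123 = 12 and 146 − 123 = 23, out of 27 per arm.

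**5. Sensitivity to location.** The article also says that "the median duration of hospitalisation in our target population is 5 days". The two location figures differ: 10^0.61 = 4.07 days, and 20% of that is 19.6 hours, whereas 20% of 5 days is the stated 24 hours. The censored share depends on which is used. All rows below have a day-4 limit.

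| Placebo median | Average censored | Power at 123 | Power at 150 | n for 80% |
|---|---|---|---|---|
| 5 days (printed) | 57% | 68% | 77% | about 163 |
| 4.07 days (10^0.61) | 44% | 73% | 81% | about 146 |
| 3 days (assumed) | 26% | 77% | 84% | about 133 |

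**6. Effect of a day-12 observation.** Keep the 12-hour grid to day 4 and add only whether cessation fell between day 4 and day 12. With log10 mean 0.61, the SE at 123 per arm falls from 0.0377 to 0.0362. Power is 76% at 123, 84% at 150 and 80% at 135.

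**The case against.** The strongest reply is that the trial enrols 300 children, not 246, and that the 22% was added partly for wrong assumptions. This stands. A reader might infer from the lost power at 123 that the margin is exhausted or that the trial falls below 80%. On the article's own mean of 0.61 neither follows: 150 per arm gives 81% to 84% before loss. The need exceeds 150 only under less favourable inputs, such as the printed 5-day median with a day-4 limit.

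A reader might also take 44% as a forecast. It is not one. Hospital stay runs from admission to discharge, while the end point runs from first dose to the start of the clean period. If the historical stays already include the diarrhoea-free day, a day-4 limit deducts that day twice, and 31% with about 76% power is the nearer figure. The discharge limit itself is also less firm than the treatment section suggests, because Data collection says discharge is arranged once the physician judges that hospitalisation is no longer needed. These two statements should be reconciled.

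The AFT model does accommodate censored times, but it does not restore the information lost. Table 1 lists a diarrhoea assessment at follow-up, which could recover part of it, but the article does not say that this feeds the primary end point. Detailed coding of unresolved discharges may properly sit in an analysis plan. The power claim for 123, however, is printed here.

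**Conclusion.** The concern holds in a limited form. The 123 per arm gives 80% power only with complete observation. Under the article's discharge rule and end point, with hospital stay as proxy and log10 mean 0.61, it gives about 76% to 73%. Across the locations and limits considered, the range is about 68% to 77% at 123 and about 77% to 84% at 150 before any loss. Built-in censoring takes somewhat under half to most of the 27 extra children per arm. On the 0.61 mean, an assumed 10% loss then leaves about 80% to 77%. The direction is the same in every case examined; the size depends on the proxy, on the day-4 or day-5 limit and on which location figure is right. This is a misstatement of power and of what the margin covers. It is not a demonstration that 300 children are too few.

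**What to change.** Neither the discharge rule nor enrolment needs to change, and the Trial status section says recruitment has not begun.

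1. **Restate the power sentence.** Say that 123 per arm assumes complete observation. Give power at both 123 and 150 per arm allowing for censoring at discharge, with the full range (about 68% to 77% and 77% to 84% before loss) and the hospital-stay proxy named as an assumption. Reconcile the log10 mean of 0.61 with the 5-day median and the 24-hour effect.
2. **Use the day-12 visit.** For children discharged without a confirmed diarrhoea-free period, do not rely on right-censoring alone. Record at the planned visit whether and when diarrhoea stopped, and enter it as an interval-censored time (about day 4 to day 12). On the 0.61 mean this gives about 76% power at 123 and 84% at 150.

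The cost is one item at a planned visit and a revised paragraph. The drawback is that the post-discharge time is coarse and parent-reported. Its use in a nurse-assessed primary end point must be squared with three places: the separate parent-recorded secondary end point, the analysis section, and the Discussion's caution about the reliability of stool-frequency data after discharge. The visit must also apply to all children: the treatment section plans it for participants at discharge, but the abstract limits follow-up visits to a subset.
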